**Methods:**

The study is an open-label cluster-randomized effectiveness-implementation hybrid trial including all 78 cardiac rehabilitation centres (attending to approximately 10 000 MI patients/year) that report to the SWEDEHEART registry. The centres will be randomized 1:1:1 to three clusters: 1) reporting cardiac rehabilitation structure and process variables to SWEDEHEART every six months (audit intervention) and being offered implementation support to implement guidelines on secondary prevention (implementation support intervention); 2) audit intervention only; or 3) no intervention offered. Baseline cardiac rehabilitation structure and process variables will be collected. The primary outcome is an adherence score measuring centre-level adherence to secondary prevention guidelines. Secondary outcomes include patient-level secondary prevention risk factor goal attainment at one-year after MI and major adverse coronary outcomes for up to five-years post-MI. Implementation outcomes include barriers and facilitators to guideline adherence evaluated using semi-structured focus-group interviews and relevant questionnaires, as well as costs and cost-effectiveness assessed by a comparative health economic evaluation.

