### The interventions

First, baseline structure and process variables will be administered through the SWEDEHEART-CR registry at all CR centres. Second, two clusters will receive one of two interventions (A and B) and one cluster will receive no intervention (control cluster) (C) (Fig. 1):

A)Reprting CR structure and process variables through the registry every six months and being offered structured implementation support (audit intervention + implementation support intervention).B)Reporting CR structure and process variables through the registry every six months but no structured implementation support being offered (audit intervention).C)No reporting of CR structure and process variables, and no structured implementation support offered (control).

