### Primary effectiveness outcome

The primary endpoint is an “adherence score”, measuring adherence to the National Guidelines on Secondary Prevention [15]. The adherence score is partly derived from the 30 variables capturing guideline-directed CR structure and processes incorporated into the SWEDEHEART-CR registry in October 2023. Permissible values are yes/partly/no/unknown. Additionally, the adherence score will include nine process variables that measure a) patient attendance in various CR components (number of patients attending a CR programme component divided by the number of patients eligible for participation), and b) time between MI hospitalization discharge and start of different CR programme components, already audited in SWEDEHEART:

*Attendance in CR components*
Proportion of patients attending an initial CR assessment (nurse visit).Proportion of patients attending an individual visit to a physiotherapist after discharge before starting an exercise-based CR (EBCR) programme (a pre-exercise screening visit).Proportion of patients completing a 3-month EBCR programme.Proportion of patients attending an individual close-out visit to a physiotherapist after completing an EBCR programme (a post-exercise assessment visit).Proportion of patients attending a patient education programme.Proportion of patients attending a close-out CR visit with a nurse at one-year after MI.*Time (days) to start of different components of CR*7.Time from hospital discharge to initial CR assessment (nurse visit).8.Time from hospital discharge to the pre-exercise screening visit to a physiotherapist.9.Time from pre-exercise screening visit to start of EBCR programme.

The responses will be pooled at each site into an adherence score for each CR centre. The contribution of each variable to the score will be weighed depending on the importance of each measurement, based on level of recommendation in European guidelines [1].

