### Secondary effectiveness outcomes

Table 2 displays secondary outcomes, encompassing both short- and long-term patient outcomes and implementation outcomes. Implementation outcomes will be based on responses gathered through the customized Normalisation Measure Development (NoMAD) questionnaire [29] and insights obtained from focus group interviews, as well as a cost-effectiveness analysis.

**Table 2 Tab2:** Secondary outcomes

Outcomes	Cluster	Measures	Data source	Timing
Short-term patient-level outcomes	All clusters	- Blood pressure (mmHg). - LDL-C (mmol/L). - Self-reported statue of health measured using EuroQol-VAS (0–10). - Self-reported smoking status (never/ prior [> 1 month smoke-free]/active) - Self-reported dietary habits (four questions with Likert scale 0–3 points, total score 0–12 points). - Self-reported physical activity (the number of days during the last week the patient has been physically active for a minimum of 30 min [at least 10 min at a time] with activity causing shortness of breath and a slightly increased pulse, corresponding to a brisk walk). - Completing an exercise-based CR programme for at least 3 months (yes/no)	The SWEDEHEART registry	Baseline and one-year after the start of intervention
		- Adherence to secondary prevention medication	Pharmaceutical registry	Baseline and one-year after the start of intervention
Long-term patient-level outcomes	All clusters	Total mortality Major adverse cardiovascular events (MACE) consisting of the following: - cardiovascular mortality - non-fatal MI - non-fatal ischemic stroke - coronary revascularization - hospitalization for new or worsening heart failure	National Patient Registry and the Cause of Death Registry	Up to 5 years after the end of the intervention
Centre-level implementation outcomes	Cluster A	- Barriers - Facilitators	Semi-structured focus group interviews	At the start and the end of implementation support period
		- Implementation cost and cost effectiveness.	A comparative health economic evaluation	At the start and the end of implementation support period

*LDL-C* low-density lipoprotein cholesterol, *VAS* visual analogue scale, *CR* cardiac rehabilitation, *MI* myocardial infarction

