### The timeline

The audit intervention started in October 2023 and will continue for 3 years. An interim analysis will be conducted two years after the start of the intervention. If the interim analysis shows the primary endpoint to be met (a difference of at least ± 2.0 in adherence score) the intervention will be terminated. Otherwise, the intervention will be continued until October 2026 and thereby uphold.

The implementation support intervention will start Q2 2024. Centres randomized to the implementation intervention will receive implementation support consecutively over a period of 18 months. The order in which centres will receive implementation support will depend on the centres’ possibilities and the research team´s capacity. The study outline is displayed in Table 3.

**Table 3 Tab3:** Flow chart for the study

**Procedure**	2023		2024		2025		2026		2030
	Q3	Q4	Q1-2	Q3-4	Q1	Q3	Q1	Q3	
Randomization	√								
Structure and process variables - intervention sites (cluster A and B)	√	√	√	√	√	√	√	√	
Interim analysis						√			
Implementation support at intervention sites (cluster A)			√	√	√				
Utility of implementation assessment (cluster A)			√	√	√				
Structure and process variables -control sites (cluster C)	√					√		√	
End of audit intervention						(√)		√	
End of follow-up									√

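### Table 2 times the short-term patient outcomes from the start of the intervention, the Abstract from each patient's MI; taken literally, Table 2 dilutes the audit comparison (B versus C)

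*Protocol article*

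**What the plan says.** In the protocol article, Table 2 (Secondary effectiveness outcomes) gives one timing for the short-term patient measures in all clusters: "Baseline and one-year after the start of intervention". The measures include blood pressure, LDL-C, smoking, physical activity, completion of exercise-based rehabilitation and medication adherence.

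Two other places use the patient's MI as the clock. The Abstract (Methods) names "patient-level secondary prevention risk factor goal attainment at one-year after MI" as a secondary outcome. Under Primary effectiveness outcome, one registry process variable is "Proportion of patients attending a close-out CR visit with a nurse at one-year after MI".

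On dates, The timeline states: "The audit intervention started in October 2023 and will continue for 3 years". It adds: "An interim analysis will be conducted two years after the start of the intervention". The audit may be stopped at that point. Data analysis compares patients at B and C centres for the audit and selects them by a minimum of two rehabilitation follow-up visits. Neither that section nor Study setting and recruitment ties patients to the start of the audit by date.

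**The concern.** The two anchors describe different patients. One year after MI follows each patient for a fixed time, whenever the MI occurred. One year after the start of the intervention is a point on the centre's calendar, and for the audit that point is October 2024. A patient seen then at the one-year visit entered rehabilitation at about the time the audit began, or earlier.

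The second secondary aim asks whether audit and feedback improves patient outcomes. If the calendar anchor is followed, the answer comes from patients with the least exposure the design can offer, in the first third of a three-year intervention. Rehabilitation that took place before the audit cannot have been changed by it, so a true effect in B would be understated.

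**Working it through.** **The plan's own figures.** The article gives no sample size or power for patient outcomes, so there is none to reproduce. Its calculation for the adherence score (23 centres per group, SD 2.4, difference 2.0) reproduces at 80.7% power by the normal approximation and does not enter this point.

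**Inputs.** Audit start is October 2023, taken as month 0, and the planned end is month 36 (The timeline). The interim is at month 24 (The timeline). The close-out visit is 12 months after MI (Primary effectiveness outcome). The exercise programme lasts 3 months (same section). MI and discharge are treated as falling in the same month, which is an assumption.

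**Step 1: who is read at month 12.** MI month = visit month − 12. A visit at month 12 gives 12 − 12 = 0, an MI in October 2023.

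**Step 2: allow for a visit window.** None is stated, so widths of 3, 6 and 12 months are assumed, with visits spread evenly, the window either closing at month 12 or centred on it. For an MI in month m, the share of the rehabilitation year under audit is (12 + m)/12 if m < 0, and 1 otherwise. A 3-month programme can have finished before month 0 only if m ≤ −3, so the last column is an upper limit.

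| Window | MI months | MI before start | Mean share of year under audit | Programme possibly finished before start |
|---|---|---|---|---|
| 3, closing | −3 to 0 | 100% | 1 − 1.5/12 = 0.875 | 0% |
| 6, closing | −6 to 0 | 100% | 1 − 3/12 = 0.75 | up to 3/6 = 50% |
| 12, closing | −12 to 0 | 100% | 1 − 6/12 = 0.50 | up to 9/12 = 75% |
| 3, centred | −1.5 to 1.5 | 50% | 1 − 0.5 × 0.75/12 = 0.97 | 0% |
| 6, centred | −3 to 3 | 50% | 1 − 0.5 × 1.5/12 = 0.94 | 0% |
| 12, centred | −6 to 6 | 50% | 1 − 0.5 × 3/12 = 0.875 | up to 3/12 = 25% |

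The missing part is always the beginning of the year, where the first nurse visit, the pre-exercise screening and the start of training lie.

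**Step 3: how far the audit has run.** Reporting is six-monthly, so at month 12 about two reports after baseline have been made (months 6 and 12). Table 3 collects cluster C's structure and process variables in Q3 2023, Q3 2025 and Q3 2026. Around October 2024 there is therefore no post-baseline set of these variables from the controls to set beside the patient results.

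**Step 4: the same dates with the MI as anchor.** Requiring discharge at month 0 or later and a one-year visit before the audit ends gives MIs in months 0 to 24 if the audit runs to month 36, and months 0 to 12 if it stops at month 24. Every such patient has the whole rehabilitation year under audit (share 1.0). At about 10 000 MI patients a year (Abstract), the ceiling is 10 000 × 2 = 20 000 or 10 000 × 1 = 10 000 over all 78 centres and all three clusters. The type 1 MI, age and two-visit rules will reduce it.

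**The case against.** The best defence is that Table 2 is loosely worded and means the one-year post-MI reading. The Abstract and the close-out visit support that. The row also covers cluster C, which has no intervention to start. If that is the intention, the dilution disappears. This part stands: the harm depends on the literal reading. However, the article uses the word intervention for the centre-level audit or support, and Table 2 also counts the long-term follow-up from the end of the intervention where the Abstract counts from MI. The literal reading is therefore a natural one and the conflict needs resolving.

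A reader might go further in three ways that the document does not support.

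- One might infer that the audit would be judged only on patients from before it began. That requires a visit window closing at month 12. No window is given, and a centred one puts about half the MIs after the start.
- One might infer that patients treated in the next two audit years would go unused. Data analysis sets no calendar cut-off that excludes them.
- One might infer that a calendar anchor leaves baseline without meaning. A cross-section of patients at audit start would be a possible baseline. For completing an exercise programme, it is the patient-level anchor that offers no individual baseline, so the repair must supply one at cohort level.

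The absence of accrual dates is not in itself a fault, because an article may leave them to the full protocol. The fault is two stated times for the same outcomes.

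**Conclusion.** The inconsistency is established: the article gives two incompatible time anchors for the short-term patient outcomes. If Table 2 is followed as written, B versus C is read around October 2024 in patients whose MI was at or around audit start. Their average share of the rehabilitation year under audit is 50% to 97% over the windows considered, with the loss concentrated in the early components. The expected bias is toward no effect. It is substantial for a 12-month window closing at month 12 and small in exposure terms for a narrow centred one, although even then the audit is only one year old.

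This rests on the outcome being the one-year post-MI visit, on visits spread evenly over the assumed window, and on Table 2 being meant literally. Only secondary outcomes are concerned; the primary adherence score and its sample size are untouched. The change should be made, but it does not threaten the trial's main result.

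**What to change.** 1. In Table 2, change the timing of the short-term patient outcomes to one year after the index MI, so that it agrees with the Abstract.
2. In Data analysis, for B versus C, include patients discharged on or after audit start whose one-year visit falls before the audit actually ends: October 2026, or earlier if it stops at the two-year interim. Tie the rule to the actual end and not to a fixed discharge date, because a fixed date could admit patients whose rehabilitation year ran on after an early stop.
3. Define baseline for the centre-level comparison as a pre-audit cohort, namely patients whose one-year visit fell before October 2023.

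The date rule in item 2 is for the audit only. Support in cluster A is staggered ("Centres randomized to the implementation intervention will receive implementation support consecutively over a period of 18 months"), so A versus B would need its own.

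The cost is a change of wording and a registry date filter, with no new data collection. Short-term results will come later than late 2024. If the audit stops at the interim, the eligible cohort is about one year of discharges instead of two, at most about 10 000 patients across all centres before the eligibility and two-visit rules.

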### Sample size calculations

As the number of CR centres is fixed, sample size calculations have been performed to estimate the difference in mean adherence score the study will be able to reveal. For this purpose, in a feasibility analysis the CR structure and process variables were collected from 8 CR centres of different sizes and geographical locations. The mean adherence score was 30.8 (standard deviation [± 2.4]) out of a maximum available score of 39. For the audit intervention, given the following presumptions:

23 out of possible 26 CR centres in each group (minimal drop-out is anticipated).Power of 80%.An alpha value of 0.05.

The study will have the power to identify a difference of ± 2.0 in adherence score between centres in cluster B (randomized to having variables on CR structure and processes incorporated in the SWEDEHEART registry) and cluster C (no new variables incorporated).

For the implementation support intervention, only centres in the lower 2 tertiles of the adherence score at baseline (approximately 17 centres) will be offered implementation support. Given the following presumptions:

14 out of possible 17 centres in each group (minimal drop-out is anticipated).Power of 80%.An alpha value of 0.05.

The study will have the power to identify a difference of ± 2.5 in adherence score between centres in cluster A (randomized to receiving implementation support) and cluster B (no implementation support).

### The timeline

The audit intervention started in October 2023 and will continue for 3 years. An interim analysis will be conducted two years after the start of the intervention. If the interim analysis shows the primary endpoint to be met (a difference of at least ± 2.0 in adherence score) the intervention will be terminated. Otherwise, the intervention will be continued until October 2026 and thereby uphold.

The implementation support intervention will start Q2 2024. Centres randomized to the implementation intervention will receive implementation support consecutively over a period of 18 months. The order in which centres will receive implementation support will depend on the centres’ possibilities and the research team´s capacity. The study outline is displayed in Table 3.

**Table 3 Tab3:** Flow chart for the study

**Procedure**	2023		2024		2025		2026		2030
	Q3	Q4	Q1-2	Q3-4	Q1	Q3	Q1	Q3	
Randomization	√								
Structure and process variables - intervention sites (cluster A and B)	√	√	√	√	√	√	√	√	
Interim analysis						√			
Implementation support at intervention sites (cluster A)			√	√	√				
Utility of implementation assessment (cluster A)			√	√	√				
Structure and process variables -control sites (cluster C)	√					√		√	
End of audit intervention						(√)		√	
End of follow-up									√

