### Quantitative data

For baseline characteristics descriptive statistics will be used (means +/-standard deviation, medians [quartile 1, quartile 3], proportions [%] and ranges). For the primary outcome analysis, given randomized treatment assignment, total adherence scores at end of follow-up as well as change in scores between baseline and follow-up will be compared using linear regression analysis. In the case of unequal randomization concerning CR centre size (small < 75 patients/year, medium 75–150 patients/year or large > 150 patients per year), geography (6 geographical districts in Sweden, two in each stratum) or the centres belonging to a university hospital (yes/no), adjusted multivariable analysis will be performed. Results will be reported as relative treatment effects (odds ratios) with 95% confidence intervals. For secondary outcome analysis on short-term patient outcomes, the same statistical methods will be used, applying linear (continuous) or logistic (binary) regression analyses. For long-term outcomes (major adverse cardiovascular events [MACE] and total mortality) Cox proportional hazards regression models will be performed, reporting hazard ratios with 95% confidence intervals. In case of missing data, imputation will be considered. For all quantitative analyses a two-sided test of statistical significance will be used with an alpha level of 0.05.

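### The interim rule stops the audit on a raw 2.0-point difference in either direction, so its error rate depends on an SD estimated from 8 centres

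*Protocol article*

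**What the plan says.** Under The timeline: "The audit intervention started in October 2023 and will continue for 3 years". One look at the data is planned before that point: "An interim analysis will be conducted two years after the start of the intervention". The stopping rule says that, should this look find "the primary endpoint to be met (a difference of at least ± 2.0 in adherence score) the intervention will be terminated". When the threshold is missed, the audit runs to October 2026. The bracket is the only definition given of the endpoint being met.

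The same 2.0 appears under Sample size calculations: "The study will have the power to identify a difference of ± 2.0 in adherence score between centres in cluster B" and cluster C. It rests on 23 centres per group, 80% power, alpha 0.05 and an SD of 2.4 from a feasibility exercise in 8 centres.

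Under Quantitative data, for every quantitative analysis, "a two-sided test of statistical significance will be used with an alpha level of 0.05". No adjustment for the interim look is mentioned.

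The audit intervention is the six-monthly reporting of structure and process variables by clusters A and B (The interventions; The audit intervention). The primary comparison for implementation support, A versus B, uses the same adherence score (Data analysis). On the schedule of that support, the text says: "Centres randomized to the implementation intervention will receive implementation support consecutively over a period of 18 months", starting in Q2 2024. Table 3 ticks it only to 2025 Q1.

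**The concern.** A detectable difference is the true effect for which a trial of a given size has a given power. It does not measure the evidence in the observed data. Used as a stopping threshold, it leaves three things open.

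- **Error rate.** A threshold fixed in points corresponds to a different p-value for every value of the SD. The plan therefore does not know its own chance of a false stop.
- **Direction.** With the ± sign, the endpoint is met as written when audited centres score 2 points worse than control centres.
- **Second look.** A final test at the full 0.05 comes on top of whatever error the interim spends.

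The decision governed by this rule is whether the audit arm of a national trial ends a year early. It also touches the second primary comparison: ending the audit ends the reporting that supplies 30 of the score's variables in A and B, and the plan does not say whether a final score would still be collected there.

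**Working it through.** **Inputs.** SD 2.4 from 8 centres, 23 centres per arm, difference 2.0, 80% power and alpha 0.05 (Sample size calculations); two-sided testing (Quantitative data). The correlation between the interim and final test statistics is not given, so I assume a range of 0 to 0.95.

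**1. Reproduce the plan's figure.** SE = 2.4 × √(2/23) = 0.708. Detectable difference = 0.708 × (1.960 + 0.842) = 1.98 (2.03 by the t-test). The stated 2.0 is right as a detectable difference.

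**2. What an observed 2.0 means at the planning SD.** z = 2.0/0.708 = 2.83, two-sided p = 0.0047 (0.0071 by t with 44 df). An observed difference of 1.39 (1.43 by t) is already significant at 0.05. With no effect, the rule stops with probability 0.0047, about 0.0024 in each direction. Adding an unadjusted final test at 0.05 gives an overall error of 5.45% at correlation 0, 5.32% at 0.5, 5.08% at 0.82 and 5.00% at 0.95.

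**3. How well the SD is known.** With 7 df and normality assumed, the 95% limits are 2.4 × √(7/16.01) = 1.59 and 2.4 × √(7/1.69) = 4.88.

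**4. The same rule at other SDs.** P(stop | no effect) = 2 × [1 − Φ(2.0/SE)], 23 per arm. The range in the last column runs over correlation 0.95 to 0.

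| True SD | SE | z at 2.0 | P(stop, no effect) | Overall two-look error |
|---|---|---|---|---|
| 2.4 | 0.708 | 2.83 | 0.5% | 5.0–5.5% |
| 3.0 | 0.885 | 2.26 | 2.4% | 5.2–7.3% |
| 4.0 | 1.180 | 1.70 | 9.0% | 9.5–13.6% |
| 4.88 | 1.440 | 1.39 | 16.5% | 16.6–20.7% |

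**5. Where 2.0 stops being significant.** Solve 2.0 = critical value × SD × √(2/23). This gives SD = 3.46 by the normal and 3.37 by the t-test, so about 3.4, which lies inside the interval in step 3.

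**6. Timing for A versus B.** By the text, Q2 2024 plus 18 months is about Q4 2025, after a stop in autumn 2025. By Table 3, support ends in 2025 Q1 and A and B report again in 2025 Q3, before or at the stop. On either schedule an early stop puts the Q1 and Q3 2026 reports from A and B in doubt. Table 3 schedules cluster C for collection in Q3 2025 and Q3 2026.

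**The case against.** The strongest reply is that on the plan's own numbers the threshold is demanding. At SD 2.4 it equals p of about 0.005, and the overall error barely exceeds 5%. That stands: a reader might infer that the rule lets the trial claim success on weak evidence as planned, and the document does not support this. Such a stop needs an SD roughly 40% above the planning value. The reply does not remove the fault, because an SD from 8 centres cannot exclude that value.

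A reader might also infer that the trial fails half the time when the true difference is 2.0, since the observed difference then reaches 2.0 with probability 50%. It does not fail. Missing the threshold only continues the audit to October 2026 and the final analysis.

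The endpoint being met could be read as also requiring the two-sided 0.05 test. The bracket does not say so, and that reading would still leave two unadjusted looks, with an error of up to 1 − 0.95² = 9.75% where the point threshold does not bind and the looks are uncorrelated. The ± may be a carry-over from the two-sided sample size statement, but as written it covers both directions. A separate analysis plan may set a boundary. The point here is the rule that the article does state.

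On A versus B, it is tempting to say that the data would be lost. The rule ends the intervention and is silent on outcome collection, reports to Q3 2025 would exist, and nine score components are already audited in the registry. The risk is truncation, and it is inferred.

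Finally, the score is to be weighted: "The contribution of each variable to the score will be weighed depending on the importance of each measurement". A reader might infer from the pilot maximum of 39 (30 + 9 variables) that the 2.0 came from an unweighted score and does not carry over. The document never says how the pilot score was weighted, so I do not rely on this.

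**Conclusion.** The concern holds in a limited form. The stopping criterion reuses a planning quantity as evidence of effect, takes no account of the standard error or of direction, and sits beside an unadjusted 0.05. The fault is that the error rate is not controlled; it is not large at the planning values. Overall error is at most about 5.5% at SD 2.4, but up to about 7% at SD 3.0, 14% at 4.0 and 21% at 4.88. All of these SDs are compatible with the 8-centre estimate. These figures assume 23 centres per arm, normally distributed scores, an unadjusted two-group comparison, and the stated range of interim-final correlation. With 26 per arm, the SD above which an observed 2.0 is not significant moves from 3.46 to 3.68 by the normal calculation.

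The consequence for A versus B is a gap in the text: the plan does not say whether the end-of-follow-up score survives an early stop of the audit.

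**What to change.** 1. Replace the point threshold with a pre-specified boundary on the B-versus-C test from the primary model, in the direction favouring B. One example is Haybittle-Peto: stop only if B is better and two-sided p < 0.001, with the final test at about 0.05. Overall error is then at most 0.05 + 0.0005 = 5.05% whatever the SD, and no information fraction is needed.
2. State that 2.0 is the detectable difference only.
3. State that an early stop of the audit does not cancel the end-of-follow-up score. Keep a single Q3 2026 collection of the structure and process variables in A and B, as Table 3 already plans for C. A single round is enough: continuing the six-monthly reporting would itself continue the audit, and the stop would then stop nothing.
4. Reconcile the 18-month support period in the text with the Table 3 ticks that end in 2025 Q1.

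The change should be made before any B-versus-C interim data are seen. **Cost:** protocol and analysis plan wording, plus one further collection round if the audit stops early. Early stopping also becomes less likely at the planning SD. The boundary sits at 3.29 × 0.708 = 2.33 points by the normal calculation, so with a true difference of 2.0 the chance of stopping falls from 50% to 1 − Φ((2.33 − 2.0)/0.708), about 32%. The final analysis is unaffected.
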